## Methods/Design

### Trial Design

Function after spinal treatment, exercise and rehabilitation (FASTER) is a multi-centre, factorial, randomised, parallel group controlled trial using validated measures of outcome and with a parallel economic analysis. It involves recruiting and consenting patients with symptoms, signs, and radiological findings of either lateral nerve root compression or disc prolapse scheduled for surgery who will be randomised using a 2 × 2 factorial design to receive:

• Factor 1 - either a six-week programme of post-operative rehabilitation or the relevant surgeon's usual postoperative care, which includes clinical review and perhaps some very limited physiotherapy:

• Factor 2 - either an educational booklet ("Your Back Operation" see below), or the surgeon's usual advice.

This will create 4 groups; rehabilitation-only, booklet-only, rehabilitation-plus-booklet, and usual care only. Allocation to a group will be stratified by surgeon and surgical procedure and allocation will use random permuted blocks within strata. This ensures that each participating surgeon and both surgical procedures will have approximately equal numbers of patients allocated to the 4 groups. Treatment allocation will be concealed to avoid selection bias during recruitment. All patients will be assessed for functional ability, pain, and satisfaction pre-operatively and then at 6 weeks, 3, 6 and 9 months and 1 year post-operatively. This will be complemented by a formal analysis of cost-effectiveness. A summary is provided in figure 1.

**Figure 1 F1:**
[figure not shown]
**Flowchart overview of the FASTER study**.

### Interventions

#### Surgical Intervention

All participants will undergo spinal surgery according to their surgeon's routine practice for that condition (i.e. either lateral or central root canal decompression or discectomy). The details of the surgical procedure performed (e.g. open versus micro-discectomy, single versus multiple levels) will be recorded as potential determinants of outcome, and a copy of the operation notes will be obtained for all patients.

#### Rehabilitation Programme

Patients randomised to the rehabilitation arms of the trial will commence the programme 6 to 8 weeks following surgery. The programme will run for 6 weeks with patients attending for 1 hour twice a week. The classes will be run by an experienced physiotherapist, who will encourage patients individually to progress at their own pace. This structure allows new patients to join the programme at any time rather than in 'batches'. There will be a maximum of ten patients per class, located at the hospital where the surgery was performed.

The classes will be standardised using the principles outlined by Frost et al [53] and will include: general aerobic fitness work; stretching; stability exercises; strengthening and endurance training for the back, abdominal and leg muscles; ergonomic training; advice on lifting and setting targets; and self-motivation. Participants will be asked to undertake shorter (30 minute) sessions of exercise at home. The classes will have a cognitive therapy basis, and will include a group discussion/open session at the end of each class where patients can discuss any problems, worries and concerns they have with each other and the physiotherapist. Compliance with classes will be recorded on the basis of attendance, and a subgroup analysis will be conducted by proportion of classes attended. In addition the classes will be reviewed regularly to ensure a uniform quality and content.

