### Trial Sample

This trial has been approved by Hammersmith and Queen Charlotte's & Chelsea Hospitals Research Ethics Committee, with site approval for Ravenscourt Park Hospital, St Mary's Hospital, St Thomas' Hospital, Royal Free Hospital, Heatherwood and Wexham Park Hospital, and Charing Cross Hospital.

Eligible patients include those currently on the waiting list for spinal surgery with either (a) signs, symptoms and radiological evidence of lateral nerve root compression, that is, patients presenting with radicular pain with an associated neurological deficit or with neurogenic claudication (pain in the buttock, thigh or leg that improves with rest), or (b) lumbar disc prolapse, that is, patients with root symptoms and signs and MRI confirmation of lumbar disc herniation. Patients with any of the following will be excluded from participation in the trial; any condition where either the intervention or the rehabilitation may have an adverse effect on the individual; previous spinal surgery; spinal surgery where a fusion procedure is planned due to the unknown hazards of the activity programme for this type of surgery; pregnant women; inadequate ability to complete the trial assessment forms; any patient who is unable to attend the rehabilitation or the reviews or who is unsuitable for rehabilitation classes.

Written informed consent will be obtained from all patients and baseline assessment completed prior to surgery and randomisation into the trial. Patients will be notified of their randomisation following surgery. Those allocated to either the booklet-only group or the rehabilitation-plus-booklet group, will get the "Your back operation" on discharge (see details below).

The trial aims to recruit 344 patients into the trial with 86 patients in each of the 4 sub-groups. This figure was based on being able to detect a 20% relative improvement in the Oswestry Disability Index (version 2.1). We anticipate a mean ODI of 40 in the control group and 32 in the exercise group at 1 year, to have a 90% chance of detecting a between-group difference of 8 points on the ODI and declaring it statistically significant using a two-sided alpha= 0.05, requires a total of 344 patients. This calculation assumes a standard deviation of 20 in each group and allows for loss to follow-up of 23%, as found in earlier descriptive work [20].

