### Proposed Analyses

Analyses will begin with a descriptive comparison of the trial groups before surgery to confirm that randomisation has produced groups that are balanced with respect to known confounders. This will include age, sex, type of surgery, ethnic background, marital status, body mass index, occupation type, work status and smoking status. Pre-operative scores on the primary and secondary outcomes will also be presented by group.

Full functional recovery from back surgery can be protracted, so the primary outcome of interest is the between-group difference in score on the ODI at one-year follow-up, based on intention-to-treat (modified to exclude patients recruited in error). Missing outcome data are expected because of this timeline. Multiple imputation under missing at random [64] will be used for patients with some follow-up but unmeasured one-year outcomes.

Groups will be compared via analysis of covariance, with adjustment for stratifying block using a linear mixed model. If assumptions appear violated, some transformation of the outcome will be taken such that assumptions appear sensible. If this fails, a non-parametric test will be used.

Parallel analyses will be performed for booklet vs. no-booklet and rehabilitation vs. no-rehabilitation, with the sample-size calculation given above applying to each of these. These calculations will be followed by an analysis which tests for an interaction of effect of the two interventions on the primary outcome.

We will check whether the same pattern of outcomes is apparent for patients undergoing lateral nerve root decompression and those undergoing discectomy, and for other subgroups defined by baseline body mass index, baseline HADS score, and single versus multiple anatomic levels of surgery. In addition to the analyses at one year, we will also compare the groups at 6 weeks (beginning of rehabilitation programme in the intervention group) and 3, 6, and 9 months.

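### Rehabilitation is given in shared, physiotherapist-led classes, but the sample size and stated model allow for no class or physiotherapist clustering; any positive correlation would understate the rehabilitation standard error

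*Protocol article*

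**What the plan says.** **Delivery (Rehabilitation Programme).** Rehabilitation is a group treatment: "There will be a maximum of ten patients per class, located at the hospital where the surgery was performed". An experienced physiotherapist runs the classes, entry is rolling, and each class ends with a group discussion. The Background explains that contact between patients is intended, because patients were thought to benefit from discussing their surgery and progress with others. The arms without rehabilitation have no such classes.

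**Sample size (Trial Sample).** "The trial aims to recruit 344 patients into the trial with 86 patients in each of the 4 sub-groups". The inputs are listed: "We anticipate a mean ODI of 40 in the control group and 32 in the exercise group at 1 year"; the aim is "to have a 90% chance of detecting a between-group difference of 8 points on the ODI", with a two-sided test at the 5% level; and "This calculation assumes a standard deviation of 20 in each group and allows for loss to follow-up of 23" per cent. No ICC or design effect appears. Proposed Analyses applies this to both factors, "with the sample-size calculation given above applying to each of these".

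**Model (Proposed Analyses).** Groups are compared by analysis of covariance, "with adjustment for stratifying block using a linear mixed model". Under Trial Design the strata are surgeon and surgical procedure. No class or physiotherapist term is named.

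**The concern.** Patients who attend the same classes under the same physiotherapist may have outcomes that are correlated because of how the treatment is delivered. That correlation would exist only under rehabilitation. A stratum term is common to both levels of the factor. It removes surgeon or hospital differences that affect everyone in a stratum, but not variation that arises only among patients who attend classes.

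If such variation exists, the confidence interval for the rehabilitation effect is too narrow and its nominal 5% test rejects too often. The claim that the sample-size calculation serves both factors equally then fails for rehabilitation. If the same model is used for the interim harm and benefit rules for rehabilitation, the understated standard error carries over to those as well.

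The booklet comparison is largely protected, because rehabilitation patients with and without the booklet join the same classes.

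**Working it through.** **1. Reproduce the stated figure.** Inputs from Trial Sample: difference 8, SD 20, two-sided 5%, power 90%, loss 23%.

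- n per level = 2 × [20 × (1.960 + 1.282)/8]² = 131.3, rounded up to 132; total 264.
- 264/0.77 = 342.9, so 343, or 344 in four equal cells. The stated figure is reproduced.
- Evaluable per level of a factor: 344 × 0.77/2 = 132.44.
- Standard error for independent patients: SE₀ = 20 × √(2/132.44) = 2.458.
- Power = Φ(8/2.458 − 1.960) = 90.2%.

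So 344 contains no hidden allowance for clustering.

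**2. Add clustering in the rehabilitation level only.** For cluster size m, the rehabilitation variance is multiplied by DE = 1 + (m − 1) × ICC and the other level is unchanged. The variance of the contrast is multiplied by A = (1 + DE)/2, and the true standard error is SE₀ × √A.

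The ICC is not in the article; 0.01 to 0.05 is an assumption. Two cluster sizes are shown:

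- m = 10, the stated maximum class size.
- m = 132.44/6 = 22.07, for one physiotherapist per hospital throughout and equal recruitment at the six hospitals listed. The article states neither.

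**3. Results.** Three quantities must be kept apart:

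- Type I error of the planned test (standard error uncorrected): 2 × Φ(−1.960/√A).
- Power of a test that uses the correct standard error: Φ(8/(SE₀√A) − 1.960).
- Rejection probability of the planned test at 8 points: Φ((8 − 1.960 × SE₀)/(SE₀√A)).

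| m | ICC | DE | A | True SE | Type I error, planned test | Power, correct SE | Rejection at 8 points, planned test |
|---|---|---|---|---|---|---|---|
| 10 | 0.01 | 1.09 | 1.045 | 2.51 | 5.5% | 89.0% | 89.7% |
| 10 | 0.02 | 1.18 | 1.090 | 2.57 | 6.0% | 87.7% | 89.3% |
| 10 | 0.05 | 1.45 | 1.225 | 2.72 | 7.7% | 83.7% | 87.9% |
| 22.07 | 0.01 | 1.21 | 1.105 | 2.58 | 6.2% | 87.2% | 89.1% |
| 22.07 | 0.02 | 1.42 | 1.211 | 2.70 | 7.5% | 84.1% | 88.0% |
| 22.07 | 0.05 | 2.05 | 1.527 | 3.04 | 11.3% | 75.0% | 85.3% |

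At ICC = 0, the stated 344 and 90% stand. The power column uses the normal quantile 1.960; small-sample degrees of freedom would lower it further when clusters are few.

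**4. Does stratum adjustment remove the effect?** This was simulated with six hospitals, four strata each, 264 evaluable patients, a stratum-adjusted model, no average treatment effect and ICC 0.05.

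- Rehabilitation-only effect at hospital level: mean model SE 2.46 against an empirical SD of 3.06; type I error 11%.
- Rehabilitation-only effect at class level, classes of up to eight: mean model SE 2.47 against an empirical SD of 2.60; type I error 6.6%.

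Additive stratum adjustment does not absorb variation confined to one arm.

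**The case against.** **The ICC is unknown.** This stands. A reader might infer that the standard error is certainly too small and the 90% certainly missed. The article does not support that: both need a positive ICC, and several features point to a small one. Patients progress individually, exercise at home and attend standardised classes that are reviewed for uniformity, and the outcome is measured at one year, months after classes end. At ICC 0.01 with classes of ten the loss is only about one point of power.

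**The larger figures need a larger cluster than the article describes.** This also stands. The article speaks of classes of at most ten, with rolling membership. Treating a whole hospital as the cluster assumes one physiotherapist per hospital for the whole trial. It also amounts to a random treatment-by-centre effect, and whether to generalise over centres is a choice of target. If rehabilitation had no effect at any site, that component would add no type I error. Nor should 75% power and 11.3% error be read as one analysis: the planned test with 11.3% error rejects 85% of the time at 8 points.

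**Covariance adjustment may recover power.** Possibly. The SD of 20 takes no credit for it, and baseline Oswestry is not named as the covariate. If used, a baseline correlation r with 1 − r² = 1/A would roughly offset the loss: r = 0.21 (A = 1.045) to 0.43 (A = 1.225) for classes of ten. It would not correct the standard error.

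**The analysis plan may add a term.** It may, and a missing model detail in a condensed article would be no finding. What remains is what the article does state: a complete calculation for independent patients, applied to both factors, and a model whose one named grouping term cannot absorb class variation.

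**Conclusion.** The point holds conditionally. Sample size and stated model treat rehabilitation patients as independent given stratum, although the treatment is delivered in groups. The direction follows for any positive ICC within class or physiotherapist; the size depends on assumptions the article does not settle.

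- Classes of ten, ICC 0.01 to 0.05: planned type I error about 5.5% to 7.7%; power with a correct standard error about 89% to 84%.
- One physiotherapist per hospital, same ICC range: 6.2% to 11.3% and 87% to 75%. This is the less favourable case and rests on the further assumption about staffing.

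The issue is confined to the rehabilitation main effect. It does not show that the trial is underpowered, and it does not call for more recruitment.

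**What to change.** 1. Record the class series or physiotherapist for each rehabilitation patient during delivery. The hospital is already known from the surgeon and attendance is recorded, but the physiotherapist may be hard to reconstruct later.
2. For the rehabilitation main effect, pre-specify a partially nested mixed model, at least as a sensitivity analysis: keep the stratum term and add a class or physiotherapist random effect that applies only in the rehabilitation arms, with small-sample degrees of freedom. Because entry is rolling, define the cluster in advance; physiotherapist is the cleaner unit.
3. Report the estimated ICC with its interval.
4. State beside the sample size that the 90% power for rehabilitation assumes no class or physiotherapist clustering, with a range such as the one above.

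The cost is one data field and one model term. The downside is a somewhat wider interval, and an imprecise variance component if there are few physiotherapists or sites. That imprecision is the reason to accept the sensitivity analysis as the minimum and not insist on a change to the primary model.

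### The planned subgroup analysis by class attendance is not a randomised comparison and can create, hide or reverse an apparent dose-response

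*Protocol article*

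**What the plan says.** The commitment stands in the protocol article under Rehabilitation Programme: attendance is recorded as the measure of compliance, and "a subgroup analysis will be conducted by proportion of classes attended".

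The same section fixes who has an attendance value and when it arises. "Patients randomised to the rehabilitation arms of the trial will commence the programme 6 to 8 weeks following surgery", and "The programme will run for 6 weeks with patients attending for 1 hour twice a week". That makes 12 classes, taken between about 6 and 14 weeks after surgery. Under Trial Design, the first factor is "either a six-week programme of post-operative rehabilitation or the relevant surgeon's usual postoperative care". Under Trial Sample, "Patients will be notified of their randomisation following surgery".

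Under Proposed Analyses, the primary result is the between-group difference in ODI at one year by modified intention to treat. That section also plans subgroups by surgical procedure and "for other subgroups defined by baseline body mass index, baseline HADS score, and single versus multiple anatomic levels of surgery". Attendance is not mentioned there. Nothing in the article describes the attendance analysis as exploratory or adjusted, or as estimated in a way that keeps the randomised comparison.

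**The concern.** The subgroups listed under Proposed Analyses rest on baseline measures or on the operation, so each has a counterpart in every allocated group. Attendance does not. It follows allocation, can depend on how the patient is recovering, and is undefined for patients not allocated to rehabilitation.

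Patients who attend most of the classes may differ from those who attend few in pain, mood, motivation and speed of recovery. Under Outcome Measures, the article itself treats anxiety, depression and fear-avoidance beliefs as possible influences on functional outcome, and the same traits could plausibly affect who keeps attending a twice-weekly class.

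At stake is how the compliance question is answered. As written, the analysis could report a gradient with attendance when the programme does nothing, or show none when it works. The reader could not tell which had happened.

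**Working it through.** **The plan's own figure.** Inputs from Trial Sample: difference 8 points (40 against 32), SD 20, two-sided alpha 0.05, power 90%, loss to follow-up 23%.

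- Per level of a factor: n = 2 × (1.960 + 1.282)² × 20² / 8² = 131.4, so 132; total 264.
- Inflated for loss: 264 / (1 − 0.23) = 342.9, so 343, or 344 in four equal groups.

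The stated 344 is reproduced. The point here does not touch it.

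**Is the comparison randomised?** Attendance is fixed only after allocation, and only two of the four groups have classes to attend. Two comparisons are possible:

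- High against low attenders, within rehabilitation: the subgroups are formed by patient behaviour, not by allocation.
- High (or low) attenders against no-rehabilitation patients: a selected part of one level is set against the whole of the other, because matching controls cannot be identified.

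The article does not say which is meant. Neither is randomised.

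**How large could the artefact be?** The document gives no correlation r between attendance and one-year prognosis, so a range of 0.1 to 0.4 in absolute value is assumed. Further assumptions: no true rehabilitation effect, SD 20, attendance treated as a normal score and split at its median.

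- The mean of a standard normal score above its median is √(2/π) = 0.798.
- High attenders against controls: r × 20 × 0.798 = 15.96 r.
- High against low attenders: twice that, 31.92 r.

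A simulation of 4,000 null trials per setting, with 132 evaluable patients per level, gave the figures in the last four columns. Differences are absolute ODI points. The percentages are the share of null trials with p < 0.05.

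| Absolute r | Formula, high vs controls | Formula, high vs low | Simulated, high vs low | p < 0.05 | Simulated, high vs controls | p < 0.05 |
|---|---|---|---|---|---|---|
| 0.1 | 1.6 | 3.2 | 3.1 | 14% | 1.6 | 8.5% |
| 0.2 | 3.2 | 6.4 | 6.3 | 46% | 3.1 | 18% |
| 0.3 | 4.8 | 9.6 | 9.5 | 79% | 4.8 | 37% |
| 0.4 | 6.4 | 12.8 | 12.8 | 97% | 6.4 | 58% |

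At r = 0 both comparisons reject in 5% of trials, as they should. The spurious gradient equals the 8-point target at r = 8 / 31.92 = 0.25.

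The simulation was run with better prognosis among attenders. The model is symmetric and the tests are two-sided, so the opposite sign gives differences of the same size in the other direction.

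**The case against.** The case on the other side is substantial.

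- **The sentence is short.** It gives no comparator, cut-point, test or causal claim, and a plain tabulation within rehabilitation would fit it. An article may leave such details to a fuller document. That stands as far as the missing detail goes. But the article does fix the classifying variable, and no choice of comparator or cut-point makes attendance a baseline characteristic.
- **The direction of bias is unknown.** A reader might infer that attenders will look better even if rehabilitation does nothing. The document does not support that: it gives no sign for the correlation. Patients who recover early or return to work may stop coming while those with persisting symptoms continue, which would hide a benefit. This objection stands in full.
- **The primary result is protected.** A reader might also infer that an attendance finding could displace a null intention-to-treat result in the conclusions. Nothing in the document suggests this. Proposed Analyses makes the intention-to-treat comparison primary and leaves attendance out.
- **The figures are unadjusted.** Pre-operative pain, HADS and fear-avoidance beliefs are collected and could explain part of the correlation. Adjustment would shrink the artefact, but it cannot be relied on to remove influences arising after surgery. The median split and normal score are also conveniences for a count from 0 to 12.
- **The instrumental-variable alternative has its own weak points.** The article does not expressly say that controls cannot join the trial classes, and usual care may include a little physiotherapy. Rehabilitation patients are also asked to exercise at home, which could affect outcome without class attendance. Both points stand and have to be met in the fix.

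**Conclusion.** The point holds. The attendance subgroup analysis conditions on a post-randomisation variable found in only two of the four groups, and it can create, hide or reverse an apparent dose-response.

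Under the assumptions shown, the artefact runs from 1.6 to 6.4 ODI points against controls and from 3.2 to 12.8 between high and low attenders, in either direction. A correlation of about 0.25 is enough to match the design target. The non-randomised nature of the comparison follows directly from the text. The size rests on an assumed correlation and is an illustration, not a forecast.

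This is a secondary analysis. The primary comparison and the sample size stand as they are.

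**What to change.** Replace the attendance subgroup analysis with a secondary complier-average causal effect estimate by instrumental variables:

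- **Instrument:** randomised allocation to rehabilitation or not.
- **Treatment received:** number of classes attended, 0 to 12. Avoid a minimum-attendance threshold, because patients below it still receive some classes and that breaks the exclusion restriction.
- **Adjustment:** stratum and pre-operative ODI.
- **Assumption to state:** allocation affects one-year ODI only through class attendance. Note that the home exercise asked of rehabilitation patients may strain this.
- **Check:** confirm from the recorded data on care received that no-rehabilitation patients attended no trial classes. If some did, enter their attendance as treatment received.
- **If the rehabilitation factor is stopped at the interim analysis:** include only patients who were randomised to that factor.

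The method compares patients as allocated, so with no effect of allocation the estimate centres on zero however attendance relates to prognosis. The result is an average effect per class; reading it as the effect of all 12 assumes linearity.

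Any table of outcome by attendance can stay if it is labelled descriptive and non-causal.

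The cost is a short change to the plan and a few hours of analysis, using attendance data already being recorded. The downside is a wider confidence interval and an assumption that cannot be tested.
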